## Abstract

**Background:**

Obsessive-compulsive disorder (OCD) is a very disabling condition with a chronic course, if left untreated. Though cognitive behavioral treatment (CBT) with or without selective serotonin reuptake inhibitors (SSRI) is the method of choice, up to one third of individuals with obsessive-compulsive disorder (OCD) do not respond to treatment in terms of at least 35% improvement of symptoms. Mindfulness based cognitive therapy (MBCT) is an 8-week group program that could help OCD patients with no or only partial response to CBT to reduce OC symptoms and develop a helpful attitude towards obsessions and compulsive urges.

**Methods/design:**

This study is a prospective, bicentric, assessor-blinded, randomized, actively-controlled clinical trial. 128 patients with primary diagnosis of OCD according to DSM-IV and no or only partial response to CBT will be recruited from in- and outpatient services as well as online forums and the media. Patients will be randomized to either an MBCT intervention group or to a psycho-educative coaching group (OCD-EP) as an active control condition. All participants will undergo eight weekly sessions with a length of 120 minutes each of a structured group program. We hypothesize that MBCT will be superior to OCD-EP in reducing obsessive-compulsive symptoms as measured by the Yale-Brown-Obsessive-Compulsive Scale (Y-BOCS) following the intervention and at 6- and 12-months-follow-up. Secondary outcome measures include depressive symptoms, quality of life, metacognitive beliefs, self-compassion, mindful awareness and approach-avoidance tendencies as measured by an approach avoidance task.

**Discussion:**

The results of this study will elucidate the benefits of MBCT for OCD patients who did not sufficiently benefit from CBT. To our knowledge, this is the first randomized controlled study assessing the effects of MBCT on symptom severity and associated parameters in OCD.

**Trial registration:**

German Clinical Trials Register DRKS00004525. Registered 19 March 2013.

## Background

Obsessive Compulsive Disorder (OCD) is a very disabling condition and the fourth most common mental illness with a lifetime prevalence of 1-3% and a 12-month-prevalence of 1-2% [1]. Individuals with OCD experience recurrent intrusive thoughts or impulses (obsessions) and/or repetitive behaviors (compulsions). If left untreated, obsessive-compulsive disorder usually takes a relapsing course and becomes chronic [2,3], associated with substantial impairment of quality of life [4,5] and limitations in social and professional life [6]. Thus, the disorder causes high costs, not only for the affected individuals but also for their families, the health system and society (see [7] for a review).

Cognitive Behavioral Therapy (CBT) with Exposure and Response Prevention (ERP) and/or pharmacological treatment with Selective Serotonin Reuptake Inhibitors (SSRI) is the evidence-based treatment of choice for patients with OCD [8,9]. For CBT with ERP, high pre-post-effect-sizes of roughly Cohen’s *d* = 1.5 and controlled effect sizes around 1.1 are reported [10]. The effectiveness of CBT with ERP is yet limited by substantial rates of patients who do not or only partially respond, suffer relapses or discontinue therapy. About thirty-five percent of the patients do not respond to the treatment recommended by current guidelines in terms of a reduction of symptom severity of at least 35% [11–13]. In addition, the probability of relapse over a 2-year period after achieving remission has been found to be 48% [14]. Especially for the subgroups of patients who do not satisfactorily benefit from CBT with ERP, complementary or alternative treatment strategies must be developed.

Mindfulness-Based Cognitive Therapy (MBCT) [15] is a manualized intervention program in an outpatient group format consisting of eight sessions. It combines mindfulness exercises with elements of cognitive therapy and has originally been designed to prevent relapse in depression. As has been shown in randomized controlled trials of two independent research groups, MBCT as an add-on to treatment as usual (TAU) reduces the probability of relapse in patients with three or more previous depressive episodes when compared to TAU alone [16–18]. A recently published study [19], however, found that MBCT reduced risk of relapse compared with treatment as usual only for participants who had experienced childhood trauma. In a study using an uncontrolled design, MBCT proved to be helpful in patients with acute depressive symptoms: Significant symptom reductions with large effect sizes have been observed after the intervention [20]. In contrast, the findings of a small randomized controlled study on MBCT in seasonal affective disorder suggest that MBCT is not effective in the prevention of disorder recurrence [21]. Several research groups have adapted the original manual for patients with other psychiatric disorders. According to current reviews, medium effect sizes for MBCT in various disorders have been found [22,23]. In randomized pilot studies, positive effects of MBCT have been demonstrated in patients with panic disorder and generalized anxiety disorder [24] and social phobia [25]. In patients with primary insomnia, symptom reductions have been observed after a treatment combining mindfulness with elements of cognitive-behavioral interventions in uncontrolled studies [26,27]. So far, however, no randomized controlled study exists concerning the application of MBCT in patients with OCD. This seems amazing, since training of paying attention to the present moment in an open, friendly and non-judgemental way as cultivated through mindfulness practice might be a powerful way for OCD patients to deal with their intrusive, unwanted and often shaming thoughts and urges [28].

In line with this, several intervention studies hint at the efficacy of mindfulness-skills in reducing OC-symptoms. In a controlled study on a student sample, subclinical OC symptoms were observed to be significantly reduced after a mindfulness training [29]. In the study by Kim and colleagues [24], in patients with generalized anxiety disorder or panic disorder, a significant decrease on the OC-scale of the Symptom Checklist-90-Revised (SCL-90-R), a self-rating instrument assessing global psychopathology, was observed. However, in this study, OC-symptoms have not been assessed with more specific instruments targeting OCD [24]. Some case studies also hint that mindfulness might be useful for patients with OCD (e.g. [30]). In a recent review, Bluett et al. [31] found that acceptance and commitment therapy (ACT), a therapeutic approach focusing on mindfulness techniques and values, was equally effective as manualized treatments such as cognitive behavioral therapy in OCD spectrum disorders.

To our best knowledge, manualized mindfulness interventions like MBCT and MBSR have not yet been investigated in controlled trials in patients with OCD at all. Besides, there are no data on the long term effects of mindfulness interventions in patients with OCD up to now, though mindfulness might be a valuable adjunct to CBT [32].

Based on these considerations, our workgroup recently conducted an open pilot study on Mindfulness Based Cognitive Therapy for patients with Obsessive Compulsive Disorder [33,34]. The intervention consisted in an 8-session MBCT program adapted to OCD [35] which closely followed the original manual by Segal, Williams, and Teasdale [15]. Qualitative and quantitative methods were used, in order to both reflect the subjective experiences of the participants with the treatment program and, on the other hand, to examine objectifiable changes in clinical symptoms. Twelve patients with residual OC symptoms after CBT completed the program and were examined immediately after the intervention and 6 months later. The results showed that MBCT was feasible in patients with acute OCD and was well accepted by the participants. From baseline to post assessment, a significant reduction of the OC symptoms (p = .008) was observed for the total scale of the Y-BOCS and the compulsions subscale (p = .004) with effect sizes within the medium range. Results remained stable at follow-up. We will therefore conduct a bicentric trial on a large sample to examine, for the first time, the effectiveness of MBCT compared to a psychoeducative program (OCD-EP) in OCD patients in order to control for unspecific group effects such as validation of experiences and mutual assistance.

## Methods/Design

### Study design

The study design is shown in Figure 1. In a prospective, bicentric, assessor-blinded, randomized, actively-controlled clinical trial, 128 patients with OCD according to DSM-IV-criteria will be randomly assigned to one of two groups: the studied intervention consists of 8 two-hour-sessions of MBCT, the control condition consists of 8 two-hour-sessions of OCD-EP. MBCT and OCD-EP will be comparable regarding treatment setting.

**Figure 1 Fig1:**
[figure not shown]
**Study design and measurement time points (CONSORT chart).** AQ-10 = autism spectrum quotient short version; AAT = approach avoidance task; BDI = Beck Depression Inventory II; BSI = Brief Symptom Inventory; KIMS = Kentucky Inventory of Mindfulness Skills; MBCT = Mindfulness Based Cognitive Therapy; MCQ-30 = Metacognitions Questionnaire with 30 Items; WST = Test of Word Power; OBQ = Obsessive Beliefs Questionnaire; OCD-EP = Obsessive Compulsive Disorder Education Program; OCI-R = Obsessive-Compulsive Inventory; SBQ-R = Suicidal Behaviors Questionnaire-Revised; M.I.N.I Mini-International Neuropsychiatric Interview; INEP = Inventory of negative effects of psychotherapy; WHOQOL-BREF = World Health Organization Quality of Life-BREF; Y-BOCS = Yale Brown Obsessive Compulsive Scale.

In the proposed trial, we hypothesize that in patients with OCD who are still symptomatic (i.e., Y-BOCS >12 points) after CBT, MBCT produces a significant reduction of OC symptoms from baseline to post assessment compared to an OCD education program (OCD-EP). A cutoff-score of 12 points is an established criterion of remission proposed by Simpson et al. [11].

The long-term outcomes of MBCT and OCD-EP six and twelve months after the interventions will be compared in an explorative manner. Means, the rates of treatment responders, the rates of patients who achieved remission and the rates of patients who relapsed will be compared. Treatment response and remission will be defined according to the criteria by Jacobson and Truax [36]. Their method includes the calculation of a) a cutoff for the symptom severity after the treatment, and b) an index for a reliable symptom improvement (reliable change index, RCI). Patients who fulfill both criteria will be classified as remitted. Patients who fulfill criterion b) will be classified as responders, even if their post-treatment score is still above the cutoff. Relapse is defined as a return to pre-treatment severity as recommended by Simpson et al. [37]. Patients who were classified as remitted after the intervention will be eligible for the analysis of relapse rates [38].

Further exploratory research questions include the effects of MBCT on secondary outcome measures such as comorbid depressive symptoms (as measured by the Beck Depression Inventory), Quality of Life (World Health Organization Quality of Life BREF), the general psychopathology (Brief Symptom Inventory), the tendency to be mindful in everyday life (Kentucky Inventory of Mindfulness Skills), distress tolerance (Distress Tolerance Scale), self-compassion (Self-Compassion Scale) and dysfunctional beliefs and attitudes (Obsessive Beliefs Questionnaire, Metacognitions Questionnaire). The relationship between mindfulness, distress tolerance and dysfunctional attitudes on the one hand and changes of clinical symptoms on the other hand will be addressed in exploratory analyses. Possible negative effects of the MBCT and OCD-EP treatment will also be explored. Additionally the change in avoidance tendencies will be assessed using an approach avoidance task (AAT) [39] measuring avoidance tendencies to contamination and checking related words and pictures. A subgroup of the sample will also take part in an additional experience-sampling task to examine changes in positive and negative affect, distress caused by OC symptoms, insight into the unreasonableness of obsessions as well as acceptance of unpleasant feelings before and after treatment. The experience sampling method (ESM) [40] is characterised by the repeated collection of real-time data on participants’ momentary inner states in their typical environments, thereby aiming to minimize memory biases and ensuring ecological validity [41].

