### Setting

Overall, eight MBCT- and eight OCD-EP-groups will be conducted (four MBCT- und four OCD-EP-groups at each site). The baseline assessments (T0) and post-assessments (T1) will be performed directly before respectively after the interventions. The first follow-up (T2) will be six months and the second (T3) will be 12 months after the end of the intervention.

The two participating centers will be the University Medical Center Freiburg and the University Medical Center Hamburg-Eppendorf. Both centers will recruit equal proportions of participants. Potential distortions due to the bicentric approach will be controlled by a stratification and by homogeneous study conditions (same room equipment, same training of the therapists, same measures, etc.).

The bicentric study was approved by the ethics commission of Freiburg University Medical Center. In accordance with the Declaration of Helsinki, all participants will be informed in detail about the design and purpose of the study. Each participant will be required to sign a written consent form and will have the freedom to withdraw consent and quit the study at any point in time. Data will be documented anonymously in a case report file (CRF), which will be stored at the University Medical Center Freiburg for 10 years. All necessary personal data will be kept confidential. All sessions will be videotaped, supervised and checked for adherence. Supervision will be provided by [name], University of Esslingen.

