### Statistical analyses

Between-group comparisons at baseline will be performed using analyses of variance for the continuous variables and Fisher’s exact test for the categorical variables. Means and standard deviations will be calculated for descriptive purposes. The main analyses will be computed using analyses of covariance in view of statistical studies suggesting that controlling for the baseline score is superior to simple pre-post comparisons and usually leads to an increase in power. An advantage of this type of analysis over mixed models is that it accounts for baseline differences and regression to the mean (i.e. higher scores usually yield greater improvement). The rates of patients achieving response and/or remission and the relapse rates in both groups will be compared using Fisher’s exact test. The time to relapse will be estimated using Kaplan-Maier survival analyses. Survival curves will be compared using a log-rank-test. A cox-regression will be performed to analyze variables influencing the time to relapse. In order to prevent distortions, the intent-to-treat principle will be used. Multiple imputation will be adopted to estimate post-treatment and follow-up scores for non-completers (i.e. no data available at reassessment). The multiple imputation principle is considered superior to the last observation carried forward method (LOCF) [64]. When using the LOCF, follow-up data can be difficult to interpret [10].

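### The exploratory relapse comparison covers only patients already remitted after treatment, so randomisation does not protect it; a sustained-remission comparison in all randomised patients should carry the between-arm question

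*Protocol article*

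**What the plan says.** All references are to the protocol article.

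- **Who is analysed.** In Study design (text after Figure 1), remission needs both a score below a cutoff and a reliable improvement: "Patients who fulfill both criteria will be classified as remitted". Only these patients enter the relapse analysis: "Patients who were classified as remitted after the intervention will be eligible for the analysis of relapse rates".
- **What relapse is.** "Relapse is defined as a return to pre-treatment severity". It can be seen only when severity is rated.
- **When severity is rated.** In Setting, after the post-assessment (T1): "The first follow-up (T2) will be six months and the second (T3) will be 12 months after the end of the intervention". No rating between these visits is stated.
- **How the arms are compared.** In Statistical analyses, "the relapse rates in both groups will be compared using" Fisher's exact test, and "The time to relapse will be estimated using Kaplan-Maier survival analyses. Survival curves will be compared using a log-rank-test". A Cox regression is planned to look for predictors of relapse timing.
- **Status.** Study design describes the 6- and 12-month comparisons, relapse included, as explorative. The confirmatory hypothesis is the change in symptoms from baseline to T1.

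**The concern.** Remission at T1 is an outcome. The plan lists remission rates among the results to compare between arms, and the trial's hypothesis is that MBCT lowers symptom severity. Selecting on remission therefore selects differently in the two arms. If MBCT brings more patients into remission, some of them will be patients who would not have remitted under the control programme, and these may be more prone to relapse. The remitters in the two arms are then no longer comparable. A Fisher or log-rank test without adjustment cannot separate this selection from an effect of MBCT on relapse.

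The likely direction is unfortunate: a treatment that helps more people can look worse at keeping them well. The multiple imputation in the plan deals with missing scores and does not address this selection.

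**Working it through.** **The plan's own figures.** No event count or power is given for relapse. The sample size rests on the primary outcome and reproduces: for *d* = 0.5, two-sided alpha 0.05 and power 0.80, the two-sample t-test needs 63.77, so 64 per arm and 128 in total. Nothing below affects it.

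**Step 1: selection with no effect of MBCT on relapse.** All inputs here are assumptions. Each simulated patient (1,000,000 draws) has one unmeasured prognostic factor *U* ~ N(0,1).

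- Remission: logit P = a(arm) − bU, with a(arm) set to give the assumed remission rate.
- Relapse by 12 months: logit P = g + bU, with the same g in both arms, set so that 30% of control remitters relapse.

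Relapse among MBCT remitters, against 30% among control remitters:

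| Remission, MBCT / control | b = 0.5 | b = 1.0 | b = 1.5 |
|---|---|---|---|
| 30% / 15% | 30.8% | 32.9% | 35.9% |
| 40% / 20% | 31.0% | 33.5% | 36.9% |
| 50% / 25% | 31.2% | 34.2% | 38.0% |

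The spurious excess runs from 0.8 to 8.0 points.

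**Step 2: the same patients with everyone counted.** In the 40% / 20%, b = 1.0 row, the share of all randomised patients who remit and stay well is 0.40 × (1 − 0.335) = 26.6% with MBCT and 0.20 × (1 − 0.30) = 14.0% with control. The all-randomised contrast favours MBCT, while the contrast among remitters points the other way.

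**Step 3: bias against chance error.** The standard error of the difference is √[p₁(1−p₁)/n₁ + p₂(1−p₂)/n₂], with 64 per arm.

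- 40% / 20%, b = 1.0 (26 v 13 remitters): √(0.335×0.665/26 + 0.30×0.70/13) = 15.7 points. The bias is 3.5/15.7 = 0.22 SE.
- 50% / 25%, b = 1.5 (32 v 16 remitters): √(0.38×0.62/32 + 0.30×0.70/16) = 14.3 points. The bias is 8.0/14.3 = 0.56 SE.

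**Step 4: how many relapses.** The Background section cites 48% relapse over two years after remission. Under a constant hazard the 12-month risk is 1 − √(1 − 0.48) = 1 − √0.52 = 0.279. With 20% to 40% of 128 remitting (assumed):

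- 128 × 0.20 = 26 remitters, 25.6 × 0.279 = 7.1 relapses
- 128 × 0.40 = 51 remitters, 51.2 × 0.279 = 14.3 relapses

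For scale, detecting a hazard ratio of 0.5 with 80% power at 1:1 allocation needs 4(1.960 + 0.842)²/(ln 2)², which rounds up to 66 events (Schoenfeld).

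**Step 5: two visits only.** Recorded relapse times can take two values, month 6 or month 12, so the log-rank test reduces to a Mantel-Haenszel test over two 2×2 tables. I simulated exponential relapse times with 30% relapse at 12 months in controls (2,000 trials per row) and assumed that no relapse resolves before the visit.

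| Setting | Times grouped at 6 and 12 months | Exact times |
|---|---|---|
| No effect, 19 v 10 | 0.056 | 0.056 |
| No effect, 64 v 64 | 0.052 | 0.054 |
| Hazard ratio 0.5, 19 v 10 | 0.139 | 0.143 |

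Entries are rejection rates at the 5% level. With equal visit schedules the test keeps its size and nearly all its power.

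**The case against.** The strongest reply is that this is an exploratory result, that whole-arm comparisons of means, response and remission at 6 and 12 months are already planned, and that the bias is small beside the chance error. All of that is right and limits the weight of the point. It does not remove it: an exploratory label tempers inference but does not make the two sets of remitters comparable, and none of the planned whole-arm comparisons measures remission that lasts.

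A reader might also infer four stronger charges, which the document does not support.

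- **That the survival analysis is invalid.** Step 5 shows otherwise for the log-rank test. What is lost is the meaning of the Kaplan-Meier curve between visits, since its steps fall on visit dates.
- **That the plan contradicts its own intent-to-treat statement.** "In order to prevent distortions, the intent-to-treat principle will be used" leads directly into imputation for patients without follow-up data, and remitters can still be analysed in their assigned arm. The fault is selection on a post-randomisation outcome.
- **That the Cox model is a flawed comparison of arms.** It is described as a search for predictors, not as the treatment contrast. Few events will limit it, but the number of covariates is unstated and a fixed limit would be a preference.
- **That the trial's main conclusion is at risk.** The primary Y-BOCS comparison does not use the remitted subset.

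The restriction is written for relapse rates. I infer that it extends to time to relapse, because relapse presupposes remission. That relapse is scored on the Y-BOCS is likewise an inference, from its role as the primary severity measure.

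**Conclusion.** The point holds, with modest weight. As written, the plan compares relapse between arms in a set chosen by an outcome that treatment is expected to change, using tests that make no allowance for that choice. The resulting bias is about 1 to 8 points against MBCT if MBCT doubles remission, relapse is 30% in control remitters and one factor drives both remission and relapse. None of these values is in the document, and a different structure could give a different size or direction. In the two scenarios worked in step 3, the standard error is about 14 to 16 points, so imprecision outweighs bias. The 7 to 14 expected relapses rest on the cited 48%, a constant hazard, assumed remission of 20% to 40%, and the cited study's notion of relapse carrying over to this trial's definition.

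The primary analysis and the sample size stand. This is a cheap improvement to an exploratory analysis, not a threat to the trial.

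**What to change.** 1. Make the between-arm comparison in all randomised patients: the proportion remitted at T1 and not relapsed at T2, and the same at T3. Patients not remitted at T1 count as failures, and missing scores are handled by the multiple imputation already planned.
2. Keep relapse among remitters, labelled as descriptive and non-randomised.
3. Report cumulative relapse proportions at 6 and 12 months, or fit a grouped-time model for the two intervals, in place of a Kaplan-Meier curve read as continuous time. The log-rank test may stay, but it adds little to the two-visit comparison.

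**Cost.** Analysis wording only, with no new data. The drawback is that sustained remission answers a slightly different question from relapse and counts patients who first remit after T1 as failures. The planned remission rates at T2 and T3 should therefore be reported beside it.
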